# Clinic-Integrated Mobile Health Intervention (“JomPrEP” App) to Improve Uptake of HIV Testing and Pre-exposure Prophylaxis Among Men Who Have Sex With Men in Malaysia: Protocol for an Intervention Development and Multiphase Trial

**DOI:** 10.2196/43318

**Published:** 2022-12-21

**Keywords:** men who have sex with men, mHealth, HIV prevention, pre-exposure prophylaxis, smartphone app, Malaysia

## Abstract

**Background:**

Men who have sex with men (MSM) are disproportionately affected by the HIV epidemic in Malaysia and globally. Cross-cutting prevention strategies such as mobile health (mHealth), particularly smartphone apps, hold great promise for HIV prevention efforts among Malaysian MSM, especially when linked to HIV testing and pre-exposure prophylaxis (PrEP).

**Objective:**

This study aims to adapt an existing app to create and test a clinic-integrated app (JomPrEP), a virtual platform to deliver HIV testing and PrEP services for MSM in Malaysia.

**Methods:**

The JomPrEP project involves developing and testing an app-based platform for HIV prevention among Malaysian MSM and will be conducted in 2 phases. In phase I (development phase), we will adapt an existing mHealth app (HealthMindr) to create a new clinic-integrated app called “JomPrEP” to deliver holistic HIV prevention services (eg, HIV testing, PrEP, support services for mental health and substance use) among MSM in Malaysia. During phase II (testing phase), we will use a type I hybrid implementation science trial design to test the efficacy of JomPrEP while gathering information on implementation factors to guide future scale-up in real-world settings.

**Results:**

As of September 2022, we have completed phase I of the proposed study. Based on a series of formative work completed during phase I, we developed a fully functional, clinic-integrated JomPrEP app, which provides a virtual platform for MSM in Malaysia to facilitate their engagement in HIV prevention in a fast and convenient manner. Based on participant feedback provided during phase I, we are currently optimizing JomPrEP and the research protocols for a large-scale efficacy trial (phase II), which will commence in January 2023.

**Conclusions:**

Scant HIV prevention resources coupled with entrenched stigma, discrimination, and criminalization of same-sex sexual behavior and substance use hamper access to HIV prevention services in Malaysia. If found efficacious, JomPrEP can be easily adapted for a range of health outcomes and health care delivery services for MSM, including adaptation to other low- and middle-income countries.

**Trial Registration:**

ClinicalTrials.gov NCT05325476; https://clinicaltrials.gov/ct2/show/NCT05325476

**International Registered Report Identifier (IRRID):**

DERR1-10.2196/43318

## Introduction

Reductions in HIV incidence and mortality have not translated uniformly on a global scale, especially in many Southeast Asian countries and among sexual minority groups, where stigma and discrimination are high [1-3]. In Malaysia, same-sex sexual behavior is illegal in both secular and Sharia laws, translating to high levels of stigma and discrimination. With over 100,000 cumulative HIV cases, Malaysia’s rapidly expanding HIV epidemic is the fifth largest in the Asia-Pacific region and has now transitioned into men who have sex with men (MSM). From 2008 to 2018, MSM accounted for an increasing proportion of incident HIV cases (10%-21.6%), with trends among this population projected to rise even more in the coming years, making MSM the primary key population with the highest HIV prevalence in Malaysia through 2030 [4,5]. Central to this expanding HIV epidemic among MSM is condomless sex, sexually transmitted infections, and co-occurring psychiatric and substance use disorders [6-9].

Modeling studies for MSM suggest that pre-exposure prophylaxis (PrEP) is a highly effective strategy to avert new HIV infections [10-18]. PrEP uptake, however, is low among Malaysian MSM despite acknowledged high risk and strong interest in taking it [19,20]. Multilevel factors undermine the scale-up of HIV testing and subsequent linkage to PrEP services among Malaysian MSM. Patient-level factors are MSM’s hesitancy to disclose their sexuality or risk behaviors in-person to providers, primarily due to fear of stigma, discrimination, or criminalization. Furthermore, findings from other studies expanded these factors to include additional patient- (eg, mental illness, negative experiences with clinicians, low perceived HIV risk), provider- (eg, stigma and discrimination), and structural-level (eg, multiple clinic visits, long waits, lack of after-hour clinic visits) barriers [21-29]. Therefore, the scale-up of HIV testing and PrEP to individuals most at risk for HIV infection requires innovations to support this marginalized group.

Mobile health (mHealth) interventions represent an innovative strategy to transform health service delivery and personal health management [23-26]. In particular, online-to-offline (O2O) models integrating emerging technologies in HIV service delivery are recommended for highly stigmatized persons with or at risk for HIV [30,31]. The O2O models represent powerful resources and opportunities to tailor online outreach as well as identify and engage key populations with a seamless transition to offline HIV clinical services. O2O, however, has often been limited by the requirement to transition to offline services, mostly in-person. Recommended innovations in O2O service delivery are the incorporation of real-time online counseling (e-Counseling) and instant text/video support via 1 platform to deliver 1 seamless, cross-channel journey experience [30].

Findings from recent studies [32,33] with MSM in Malaysia indicate that nearly the entire subgroup (>97%) owns a smartphone, with higher (89.4%) internet penetration mostly through smartphones [34]. Importantly, most MSM prefer to interface with “apps,” instead of face-to-face interaction with a clinician, to access HIV prevention and other support services (eg, substance use, mental health) [33]. Although app-based platforms are evolving to increase uptake and adherence to PrEP, most, if not all, are limited to high-income countries. In addition, no mHealth apps that provide comprehensive HIV prevention services are clinically integrated. Innovations through these apps that provide the entire clinical experience, from risk assessment, HIV self-testing, and assessing PrEP eligibility and prescription, expand the benefits of these apps, especially in settings where MSM are highly stigmatized and discriminated against [35,36]. We, therefore, aimed to adapt and test an existing app that integrates clinical services, which we call “JomPrEP,” to promote the HIV prevention cascade among MSM in Malaysia.

## Methods

### Multiphase Study Design

The proposed study, which involves developing and testing JomPrEP among Malaysian MSM, will be conducted in 2 phases. In phase I (development phase), we will adapt an existing mHealth app (HealthMindr) [37,38] to create a new clinic-integrated app called “JomPrEP” to deliver holistic HIV prevention services (eg, HIV testing, PrEP, support services for mental health and substance use) among MSM in Malaysia. During phase II (testing phase), we will utilize a type I hybrid implementation science trial design [39] to test the efficacy of JomPrEP while gathering additional information on its implementation to guide future scale-up in real-world settings. JomPrEP is being adapted to the Malaysian context from the HealthMindr app [30], developed to improve HIV testing and PrEP uptake among MSM in the United States.

### Theoretical Framework

The HealthMindr app is based on the Social Cognitive Theory (SCT) [40], which asserts that cognition, behavior, and environmental influences interact with and reinforce one another to impact health behavior. It specifies goal setting, self-efficacy, outcome expectations, and self-regulation as essential influences of health behavior. Features in HealthMindr fit the framework for several health behaviors such as making HIV testing plans, consistently using condoms, screening for PrEP, and seeking PrEP (if eligible). For each health behavior, there are specific app features designed to promote goal setting, self-efficacy, outcome expectations, and self-regulation. For example, for HIV testing, the “Make a Plan” feature promotes goal setting. The presentation of several testing options and information promotes self-efficacy, while information about the benefits of testing promotes positive outcome expectations, and a customizable reminder is used for testing self-regulation. HealthMindr has shown preliminary acceptability and usability among MSM in the United States [37], and HealthMindr combined with in-app prevention messages doubled HIV testing and PrEP uptake in a randomized trial among MSM in the United States [41]. As JomPrEP will be adapted from HealthMindr, its main domains will coincide with the core elements of the SCT framework.

### Community Advisory Board

We have instituted a community advisory board (CAB; n=8) comprising representatives from rural and urban settings, including researchers, MSM, clinical providers, and leaders of MSM-serving community-based organizations. The CAB is instrumental in collaborative work in the region and is heavily engaged in JomPrEP development and dissemination. Specifically, the CAB meets quarterly to assist in the design and content development of the platform. In addition, the CAB guides and assists the research team with (1) community outreach and study promotion; (2) fostering cross-collaboration between stakeholders and other disciplines working to improve MSM health outcomes; (3) ensuring cultural competency throughout various aspects of the study; (4) encouraging community participation in the proposed project; and (5) assistance in developing dissemination strategies, including communication of results in community forums, and feedback on adaptations to inform a future trial.

### Phase I: Development of JomPrEP

#### Overview

We will use the modified Intervention Mapping Adapt model [42] to adapt the HealthMindr app to create JomPrEP for optimal use among MSM in the Malaysian context. The modified Intervention Mapping Adapt model consists of the following sequential steps.

#### Phase IA: Theater Testing

We will conduct theater testing to examine attitudes toward the format, content, and features of HealthMindr and to receive feedback for improving the acceptability and feasibility of the newly created app. We will also explore preferences for additional features to facilitate and improve self-care, peer support, and screening and referrals for psychiatric and substance use disorder. We will conduct focus groups (FGs) with 25 MSM and 10 stakeholders. Eligibility criteria for MSM will include being (1) 18 years of age or older; (2) self-identified as MSM; and (3) able to understand English or Bahasa Malaysia. Participants will be recruited using advertisements on geosocial networking apps for MSM (eg, Grindr, Hornet) and popular social networking websites (eg, Facebook). Stakeholders will include doctors, nurses, pharmacists, mental health counselors, community outreach workers, and nongovernmental organization (NGO) staff involved in providing HIV-related services to the target population. We will start with 5 FGs (with 6-8 participants per group), each lasting approximately 60 minutes [43]. We will recruit further if saturation is not achieved.

An interview guide will be created by the investigator team. At the beginning of the theater testing session, participants will interact with HealthMindr with guidance from facilitators. Feedback will be elicited on the overall appearance and functionality of HealthMindr interface, appeal, and usability; components they like or dislike; and areas for improvement. Furthermore, participants will provide insight into the potential functionalities and content for JomPrEP in terms of addressing barriers and facilitators to HIV testing, PrEP, and substance use disorder screening and related services. For example, we intend to incorporate elements that allow participants to use the app to access HIV prevention services virtually (PrEPxpress). We will, therefore, explore options to simplify the process of accessing PrEP through a proposed “PrEPxpress” pathway that involves replacing in-person clinician interactions with virtual or home-based ones (eg, app-based risk assessment, scheduling appointments, electronic consultations [e-consults], mail-in-order for HIV testing kits, and PrEP medication).

Using findings from the theater testing, we will carefully adapt, expand, and refine the content and functionalities of the HealthMindr app to create an interactive prototype of the JomPrEP app (alpha version) while maintaining fidelity to its core elements and underlying conceptual framework. The app development team will update the interactive wireframe through multiple iterations, which will act as a skeleton for JomPrEP.

#### Phase IB: Alpha Testing

In this phase, we will conduct alpha testing of the interactive prototype developed from the previous phase to identify use-related issues that are due to the original design and missing content. Participants will also provide feedback on how each function can be used, their willingness to use it, and suggestions for improvement. It is a widely used user-centered design methodology incorporating an iterative process of testing an app’s user preferences and then applying the results to redesign the prototype to meet user needs.

We will conduct individual 1-on-1 sessions with 10 MSM and 10 stakeholders. Screening, eligibility criteria, and enrollment will be identical to procedures used for phase IA (ie, theater testing). During each session, video recordings will be made of the participant’s use of the app wireframe and voice. Each participant will be asked to complete prespecified tasks (eg, set up a profile, complete an HIV risk assessment, send a message to the clinical staff via the app, order an HIV self-testing kit, schedule an appointment for a PrEP consultation, set up a reminder for PrEP, and complete a PrEP medication order) on the app wireframe while “thinking aloud” and narrating their thoughts. Participants will then be asked to complete a questionnaire on 2 main aspects: (1) experiences with the testing; and (2) experiences completing the given tasks using the wireframe. Besides, a series of open-ended questions related to ease and experience of use, recommendations for modifications, and feasibility will be asked after completing the assigned tasks. The app developer will review the video to assist with interface changes based on participant feedback.

Based on the findings from the alpha testing, recommendations for modifications will be compiled and discussed with the app developer. The prototype will then be modified to address the key usability barriers and participant preferences. Following wireframing and alpha testing, the user interface (ie, colors and branding) will be applied to the prototype, followed by the final development of JomPrEP (beta version).

### Expected Elements of JomPrEP (Beta Version)

#### Core and Additional Features

JomPrEP will minimally include core features (refined for the Malaysian context) present in HealthMindr (eg, risk assessment, HIV testing plan, reminders, ordering of testing kits) plus additional features to virtually access HIV prevention services (ie, PrEPxpress—a clinic-integrated enhancement), such as appointment booking for HIV testing and PrEP services, a chat function to communicate with clinical staff, and a test result feature that enables participants to access their laboratory results. More features embedded in the app include e-consults, health product ordering, discrete door-to-door delivery, and notification customization. Upon downloading the app, the user completes an onboarding process, which includes creating log-in credentials. Participants are then taken to the JomPrEP landing screen with icons for key functions of the app. In addition, we will work with a few local clinics to integrate the JomPrEP platform into their existing clinical care setting. This will enable the JomPrEP users to access HIV prevention services via the app.

#### Phase IC: Beta Testing

After adaptation and refinement as described in phase IA (theater testing) and phase IB (alpha testing), beta testing of JomPrEP will be conducted to assess its usability and acceptability with Malaysian MSM. Beta testing of the app (n=50) will also help identify potential bugs and ensure its usability in a real-world setting [43]. Screening, eligibility criteria, and enrollment will be identical to the procedures used for phase IA (ie, theater testing).

All enrolled participants will be given a brief overview of the purpose of the study, followed by a survey that focuses on participant characteristics and barriers to accessing HIV testing, PrEP, and psychiatric and substance use disorder support services. The participants will then be observed downloading JomPrEP and instructed with a brief tutorial about the onboarding process. To restrict access to JomPrEP during beta testing, a single-use registration code will be provided to study participants that will need to be entered to gain access to the app. The participants will be told to keep the app for 30 days and encouraged to use all the app’s features. On day 30, the participants will be asked to provide a synthesis of issues that have emerged regarding the app and will complete a postsurvey, which will include the same questions as the presurvey and the Systems Usability Scale [44], a validated measure that assesses the subjective usability of an app. We will also collect app analytics, such as the number of log-ins, session duration, pages visited, and frequency and duration of use for each app’s components. In addition, participants will be asked to provide qualitative feedback on functionality, performance, errors encountered, motivation to use the app, overall experiences using the app, input for further refinement, and subjective impact of the app on HIV prevention outcomes. The findings from the beta testing will allow us to make final refinements to JomPrEP before the initiation of the efficacy trial (testing phase).

### Phase II: Testing of JomPrEP

#### Overview

We will conduct a type I hybrid implementation science trial [39] that involves an assessment of the efficacy of JomPrEP while assessing contextual implementation factors to guide its future adoption and scale-up. While assessing efficacy outcomes for JomPrEP, we will interview stakeholders (eg, patients, clinicians, counselors, administrative staff) to understand barriers and facilitators to JomPrEP adoption and scale-up, especially for applicability to new sites in low- and middle-income countries (LMICs).

#### Phase IIA: Efficacy Trial of JomPrEP

##### Study Design

We will conduct a prospective randomized controlled trial to evaluate the efficacy of JomPrEP versus treatment as usual (TAU) among MSM in Malaysia for primary (ie, HIV testing and PrEP uptake) and secondary (ie, PrEP adherence and persistence) outcomes over 9 months of observation. We will enroll 268 participants who will be randomized (1:1) to receive either JomPrEP or TAU and will be followed for 9 months (assessments at 3, 6, and 9 months; Figure 1).

**Figure 1 figure1:**
[figure not shown]
Study design of the JomPrEP efficacy trial (phase IIA). PrEP: pre-exposure prophylaxis; TAU: treatment as usual.

##### Study Settings and Participants

Eligibility screening and recruitment will be identical to procedures used for phase I. We will partner with the Centre of Excellence for Research in AIDS (CERiA) at the University of Malaya, Kuala Lumpur, Malaysia. Eligibility criteria will include the following: (1) age ≥18 years; (2) cis-gender men; (3) laboratory-confirmed HIV negative status; (4) no existing use of PrEP; (5) own a smartphone; and (6) ability to understand, read, and speak English. Participants will be discontinued from the study under any of these circumstances: (1) acquisition of HIV infection (will be referred to appropriate care); (2) participant voluntarily chooses to leave the study; and (3) the provider thinks the study is no longer in the best interest of the participant.

Participants will be recruited using both in-person and online recruitment strategies. For in-person recruitment, flyers will be given out to potential participants as well as posted at local community-based organizations. In addition, various general and MSM-specific social media and other online platforms will be chosen as venues for participant recruitment. These include placing advertisements in geosocial networking apps popular among MSM in Malaysia (eg, Grindr, Hornet) as well as posting study flyers on Malaysian MSM–focused Facebook pages. The recruitment materials will include brief information about the study and contact information (and a link to the study website) where potential participants could receive more information.

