##### Minimizing Contamination Across Groups

Contamination will be minimized in several ways: (1) only individuals enrolled in the project will be provided with a single-use code to access the app; (2) couples and housemates will be randomized together; and (3) participants will be assessed at follow-up about their observation of others using the app. We will disguise these questions by asking (1) “Have you seen a different version of the app?”; (2) “Do you have a buddy who is also in the study but uses a different version of the app?”; and (3) “Did you find how different is your app from others?”

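### The phase II eligibility list does not exclude men who used the working JomPrEP app in beta testing, so former testers could be randomized to either arm

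*Protocol article*

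**What the plan says.** Study Settings and Participants (phase IIA) opens with "Eligibility screening and recruitment will be identical to procedures used for phase I". The criteria that follow are "1) age ≥18 years; (2) cis-gender men; (3) laboratory-confirmed HIV negative status; (4) no existing use of PrEP" and then "5) own a smartphone; and (6) ability to understand, read, and speak English". Earlier study participation and earlier app use are not mentioned.

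Phase IC: Beta Testing describes the exposed group: "Beta testing of the app (n=50) will also help identify potential bugs", and "The participants will be told to keep the app for 30 days and encouraged to use all the app’s features". Each tester entered with a single-use registration code. Phase IC took its screening and enrolment from phase IA, which advertised on Grindr, Hornet and Facebook. Phase II names the same three and adds in-person flyers.

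Under Procedures, control participants also receive JomPrEP, with its main features switched off. Minimizing Contamination Across Groups lists three measures. The first is that "only individuals enrolled in the project will be provided with a single-use code to access the app". The second is joint randomization of couples and housemates. The third is a set of disguised follow-up questions, one of which asks whether the participant has seen another version of the app.

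**The concern.** The comparison is full app against stripped app. The plan treats knowledge of the other version as a threat, since it restricts codes and disguises its contamination questions. A man who used the full app in phase IC has already passed that barrier. Randomized to control, he can recognise what has been removed and may keep some benefit of the earlier exposure.

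Two things are at stake.

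- **The effect estimate.** If earlier exposure changes later behaviour, former testers contribute less contrast between the arms than app-naive men do. The criterion "4) no existing use of PrEP" removes testers who are on PrEP at screening. It does not remove those who used only the app or its HIV testing features, and HIV testing is also a primary outcome.
- **The contamination measure.** A former tester in the control arm can truthfully say that he has seen a different version although nothing has leaked between the arms. His answer cannot be told apart from real contamination.

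**Working it through.** **Does anything in the article close this route?** Going through the relevant sections:

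- *Eligibility list:* age, gender, HIV status, PrEP use, smartphone, English. No item on earlier app use.
- *Recruitment:* the online channels overlap with those of phase I.
- *Timing:* phase I was complete as of September 2022 and phase II was to start in January 2023, so exposure would be recent for early recruits.
- *Contamination measures:* code restriction, joint randomization and follow-up questions. None acts on exposure before enrolment.

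The route is open as printed.

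**Inputs for the size** (Sample Size; Phase IC): PrEP uptake 50% in control and 60% with JomPrEP, 121 per group, 1-sided 0.05, 268 randomized 1:1, 50 beta testers.

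**The plan's own figure first.** The usual pooled formula for two proportions is

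n = [1.645·√(2·0.55·0.45) + 1.282·√(0.50·0.50 + 0.60·0.40)]² / 0.10² = (1.157 + 0.897)² / 0.01 ≈ 423 per group.

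The stated 121 per group does not reproduce. At 50% versus 60% it has power Φ[(0.10·√121 − 1.157)/0.70] = Φ(−0.082) = 46.7%. With 121 per group, 90% power needs about 50% versus 68.3%. That is a separate and much larger matter, not caused by the present point. It is noted here only because it sets the starting row of the table.

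**Dilution model.** Let k former testers enrol and let f = k/268. Randomization makes f the expected share in each arm. Let c be the carry-over, meaning the fraction of the planned effect that a former tester in the control arm already has. Then

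- control uptake = 0.50 + 0.10·c·f
- difference = 10·(1 − c·f) points.

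Neither k nor c is in the documents, so both are assumed. The table takes the worst case, c = 1, and assumes that former testers drop out at the same rate as other men. The last column repeats the exercise for a true effect of 18.3 points, the size that 121 per group can detect with 90% power.

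| k | f | Difference, planned 10 points | Power at 121 per group | Power if the true effect is 18.3 points |
|---|---|---|---|---|
| 0 | 0% | 10.0 | 46.7% | 90% |
| 5 | 1.9% | 9.8 | 45.6% | 89.0% |
| 10 | 3.7% | 9.6 | 44.4% | 88.0% |
| 25 | 9.3% | 9.1 | 41.0% | 84.4% |
| 50 | 18.7% | 8.1 | 35.5% | 77.1% |

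With half carry-over (c = 0.5) and all 50 re-enrolling, the difference is 10·(1 − 0.5·0.187) = 9.1 points. With 10 re-enrolling it is 10·(1 − 0.5·0.037) = 9.8 points.

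No expected HIV testing proportions are given, so the effect on that outcome cannot be sized.

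**The case against.** The strongest reply is that this is an omission in a condensed article. The list is introduced as what eligibility will include, which need not be exhaustive. It does not even state sex with men as a criterion. A fuller protocol may bar phase I participants, and nothing in the article says that they will be re-enrolled. This limits how firmly the point can be put. It does not remove it: the article prints a specific criteria list and a section on contamination, and both leave the route open.

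Several stronger readings are tempting and are not supported:

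- *That the opening sentence admits phase I men.* It describes procedures. The point rests on the list after it.
- *That re-enrolment would bias the trial or leave it unable to answer its question.* Randomization spreads former testers over both arms on average. The expected harm is attenuation, not systematic imbalance.
- *That the effect must be toward zero.* A former tester who finds features missing might be discouraged, which would widen the difference. One who returns to the full app might use it more fluently.
- *That the PrEP criterion leaves only men in whom the app has failed.* Thirty days is too short to say so. The argument also sits badly with counting the same men as carrying a benefit into the control arm.

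Complete carry-over is itself extreme. Most of the intervention is live service (kit ordering, e-consults, electronic scripts, delivery, reminders), and control participants lack these for all 9 months whatever they used before. The follow-up question has no time limit, so it might flag some former testers, but it cannot separate them from men exposed during the trial.

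**Conclusion.** The gap is real as printed: former phase IC testers are eligible for either arm, and no listed safeguard removes them. The likely consequence is small. At the ceiling, which needs all 50 testers to re-enrol and keep the full benefit, the planned 10 points become about 8.1. With 5 to 10 testers they become about 9.8 to 9.6, a loss of roughly 1 to 2 percentage points of power. These figures rest on an assumed number of re-enrolments and an assumed carry-over, and their direction is plausible but not certain. The confusion of the contamination question needs no carry-over assumption, only that some former testers enrol.

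This is a cheap improvement. It would not by itself put the trial's conclusion in doubt.

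**What to change.** Add to the phase II criteria: *no previous use of the JomPrEP app (phase IC beta testing)*. Check it at screening against the phase IC registration-code list and with one screening question.

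If the sponsor prefers to admit these men, record earlier app use at baseline, run a sensitivity analysis without them, and read the contamination answers with that variable in hand.

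The ten men who took part in phase IB need not be excluded: they did set tasks on a wireframe in a single session and did not receive the intervention.

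The cost is one eligibility line and one screening question. At most about 50 men leave the recruitment pool, and some of them may be ineligible already on HIV status, PrEP use or language.
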